## Abstract

**Background:** Non-motor symptoms such as sleep disturbance, cognitive decline, fatigue, anxiety, and depression in Parkinson’s disease (PD) impact quality of life. Increased levels of pro-inflammatory cytokines in individuals with PD have been reported, which may contribute to non-motor symptoms. A mind-body exercise, Qigong, has demonstrated benefits across different medical conditions. However, a lack of evidence causes clinicians and patients to be uncertain about the effects of Qigong in individuals with PD. This study will examine the effects of Qigong on non-motor symptoms and inflammatory status in individuals with PD. **Methods:** Sixty individuals with PD will be recruited. Qigong and sham Qigong group (n = 30 for each) will receive a 12-week intervention. Participants will practice their assigned exercise at home (2×/day) and attend routinely group exercise meetings. **Results:** Clinical questionnaires and neuropsychological tests will measure non-motor symptoms including sleep quality (primary outcome). Biomarker assays will measure inflammatory status. A two-way mixed-design analysis of variance (ANOVA) will be utilized. **Conclusions:** This study may generate evidence for the benefits of Qigong on non-motor symptoms of PD and the effect on inflammatory status. Findings may lead to the development of a novel, safe, and cost-effective rehabilitation approach for individuals with PD.

## 1. Introduction

Parkinson’s disease (PD) is a neurodegenerative disorder leading to both motor and non-motor symptoms. Motor symptoms, such as resting tremor, rigidity, bradykinesia, and postural instability, have traditionally drawn more attention from clinicians and researchers. Growing evidence suggests that non-motor symptoms can significantly impact quality of life, cause disability, and result in more health-related issues than motor symptoms [1,2,3]. Non-motor symptoms such as sleep disturbance, cognitive decline, fatigue, anxiety, and depression are commonly reported by individuals with PD [4]. A previous study indicated that 21% of individuals with PD reported non-motor symptoms in the early stage of PD, but this number increased to 88% seven years after diagnosis [5]. Sleep disturbances such as insomnia, restless leg syndrome, hypersomnia, and rapid eye movement sleep behavior disorder are particularly common in PD and reported to occur in 60% to 98% of individuals with PD [6]. As the disease progresses, individuals with PD show increased sleep latency and decreased total sleep time, deep sleep time, rapid eye movement sleep time, and sleep efficiency [7]. A common sleep disturbance in PD, rapid eye movement sleep behavior disorder, is associated with other non-motor symptoms including cognitive abnormalities [8,9]. Thus, improvement of sleep quality may help to increase quality of life and alleviate other symptoms in individuals with PD.

Neurodegeneration is caused by multiple contributors such as genetic, biological, and environmental factors [10]. Neuroinflammation, activated by microglial and immune cells in the brain, is one of the main contributors to neurodegeneration in PD [11]. Increased levels of neuroinflammatory biomarkers such as inflammatory cytokines in PD were reported in previous studies [12,13,14,15]. A postmortem PD brain study reported that the levels of interleukin (IL)-1β, IL-6, and tumor necrosis factor (TNF)-α were significantly increased in the cerebrospinal fluid [12]. In vivo, higher levels of IL-1β and TNF-α were found in individuals with PD compared to the healthy controls [13]. Other in vivo studies also showed increased levels of IL-6 and TNF-α in serum collected from individuals with PD [14,15].

Although it may be impossible to stop neurodegeneration in PD, many therapeutic approaches have been developed to alleviate symptoms in PD. Qigong is a mind-body exercise that has shown benefits on symptoms in PD. A study involving individuals with mild to moderate PD demonstrated a significant improvement in sleep quality [16]. In our feasibility study in a single-arm design (n = 7), a 6-week Qigong exercise program demonstrated an improvement in sleep quality measured by Parkinson’s Disease Sleep Scale-2 (PDSS-2), in which the results showed sub-scores of PDSS-2 were significantly improved or showed a trend of improvement including motor symptoms at night (*p* < 0.05) and disturbed sleep (*p* = 0.06) in individuals with PD [17]. Our recent pilot study, a randomized controlled trial (RCT), in individuals with PD showed a significant improvement in sleep quality, including PD symptoms at night (*p* < 0.05) and total PDSS-2 score (*p* < 0.001), after practicing the Qigong exercise for eight weeks (2-week training + 6-week Qigong exercise) [18].

The exact mechanism of Qigong exercise behind clinical improvements observed in patients with PD has not yet been completely understood. A possible mechanism of Qigong exercise may involve biological pathways related to neuroinflammation. The deep abdominal breathing may stimulate serotonin pathways by stimulating enterochromaffin cells that release serotonin [19] and interact with pro-inflammatory cytokines that contribute to neuroinflammation in the brain [20]. Our recent pilot study suggested potential benefits of Qigong exercise through changes in inflammation status, in which the results showed a significant decrease in serum level of TNF-α from 13.8 ± 0.6 to 12.3 ± 1.6 (*p* < 0.05) that was significantly correlated with changes in sleep quality and serum TNF-α level (R^2^ = 0.62) [18]. In various medical conditions, mind-body exercises such as Yoga, Tai Chi, and Qigong improved the immune system [21]. Particularly, past studies reported the benefits of Qigong exercise on immunological functions in healthy people [22] and individuals with cancers [23,24,25]. 

For the PD population, many studies were performed to investigate the effects of Qigong on motor symptoms in individuals with PD. However, to the best of our knowledge, only four RCTs have studied the effects of Qigong on non-motor symptoms in individuals with PD [16,18,26,27]. In those previous studies, although the results showed a potential of Qigong exercise to improve non-motor symptoms in PD, there was missing information such as rationale for sample size estimation, selection bias, attrition bias, and participant blindness. Moreover, past studies did not systematically explore the underlying mechanism of Qigong exercise for improving non-motor symptoms in PD, which may make clinicians hesitate to recommend Qigong exercise for their patients [28].

In this study protocol, we mainly discuss the rationale and research design of the study. The study aims to examine the efficacy of Qigong exercise on non-motor symptoms and neuroinflammatory status in PD. We hypothesized that Qigong exercise will improve non-motor symptoms such as sleep disturbance (primary outcome), cognitive decline, fatigue, pain, mood, and quality of life, and decrease serum levels of pro-inflammatory cytokines including IL-1β, IL-6, and TNF-α in individuals with PD. In addition, this study explores the relationship between changes in non-motor symptoms and changes in inflammatory status.

## 2. Study Design and Aims

### 2.1. Study Design

We designed a double-blind RCT involving 60 individuals with PD (Figure 1). The participants will be randomly assigned to either an experimental (n = 30) or control (n = 30) group. Each group will have group exercise meetings (nine times in total; weekly meeting for first six weeks and then biweekly meetings for next six weeks) throughout the 12 weeks of the intervention period. Participants will be blinded to their group assignments until the end of the study. At baseline, all outcome measures and demographic variables including age, sex, ethnicity, years of education, disease duration, and medications will be collected. After the baseline assessments, participants in both groups will have a 12-week intervention period, including three weeks of training and nine weeks of exercise. The duration of the intervention will be longer than our two previous studies to provide more structured training sessions and longer intervention time [17,18]. During the training period, participants in the experimental group will learn the Qigong exercise, whereas those in the control group will learn the sham Qigong exercise. During the exercise period, participants will continue to practice what they will have learned during the training period. Throughout the 12-week intervention period, all participants will be asked to perform their assigned exercise (Qigong or sham Qigong exercise) twice a day at home, in the morning and evening, attend group meetings (weekly meeting for first six weeks and then biweekly meetings for next six weeks) and keep an exercise diary. The exercise diary includes daily checklists (morning exercise (yes/no), evening exercise (yes/no), and other exercise more than 0.5 h (yes/no)), subjective scales (sleep quality (1–5), fatigue level (0–10), and pain level (0–10)), and participant’s note for any unusual events. Within two weeks after the completion of the 12-week intervention, post-intervention assessments will be conducted, which are the same as the baseline assessments. The assessments will be completed again six months after the end of the intervention period.

### 2.2. Specific Aims

Specific aim I. To examine the effects of Qigong exercise on non-motor symptoms in PD.

Primary hypothesis: Participants will have greater improvement in sleep quality after Qigong exercise than the participants after sham Qigong exercise.

Secondary hypothesis I: Participants will have greater improvement in cognitive function, fatigue, anxiety, depression, overall non-motor symptoms, and quality of life after Qigong exercise than the participants after sham Qigong exercise.

Specific aim II. To examine changes in inflammatory biomarkers in serum after practicing Qigong exercise.

Secondary hypothesis II: Participants will have greater reduction in levels of inflammatory biomarkers (IL-1β, IL-6, and TNF-α) after Qigong exercise than the participants after sham Qigong exercise.

Specific aim III. To examine relationships between changes in non-motor symptom scores and changes in the inflammatory status in PD after the intervention (both Qigong and sham Qigong).

Secondary hypothesis III: Changes in non-motor symptom scores will significantly correlate with changes in levels of the inflammatory biomarkers.

### 2.3. Ethics Approval and Informed Consent

The study protocol and the consent form were approved by the Institutional Review Board of the University of Kansas Medical Center. The study ID is #STUDY00140835. This study is registered at www.clinicaltrails.gov (NCT03463330) [29].

### 2.4. Study Criteria

#### 2.4.1. Inclusion Criteria

The study inclusion criteria include (Table 1): (1) diagnosis of idiopathic PD according to the United Kingdom Parkinson’s Disease Brain Bank Society diagnostic criteria [30], (2) women and men aged 40 to 75 years, (3) currently taking levodopa with some improvement in motor symptoms, (4) levodopa dose has been stable for a minimum of four weeks prior to the start of the study, and (5) Hoehn and Yahr stage I to III (mild to moderate PD).

#### 2.4.2. Exclusion Criteria

The study exclusion criteria include (Table 1): (1) Mini Mental State Examination score <24 [31], (2) neurological diseases other than idiopathic PD including other forms of parkinsonism, uncontrolled or significant cardiovascular diseases, orthopedic, balance, or medical problems, (3) prior major head trauma with loss of consciousness, (4) deep brain stimulation, and (5) expected change in PD medications or non-motor symptom medications (e.g., sleep, anxiety, and depression medications) that may affect the results of the proposed outcome measures over the course of the study.

#### 2.4.3. Withdrawal/Termination Criteria

The withdrawal or termination criteria include: (1) death, (2) withdrawal of consent for any reason, (3) physician discretion, (4) major changes in PD medications or other non-motor symptom medications; and (5) failure to comply (due to hospitalizations, vacations, etc.) with prescribed exercise.

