## 5. Sample Size Estimation, Statistical Methods, and Reporting Results

### 5.1. Sample Size Estimation

A total of 60 participants will be recruited. The estimation of sample size was based on 80% statistical power regarding one of the primary variables, overall sleep quality (PDSS-2 total score). In our preliminary study, we observed a significant change after Qigong exercise in overall sleep quality by 11.5 points between two groups (experimental vs. control). A pooled standard deviation between two groups was 10.7. With a statistical power of 80% and a Type I error rate at 0.05, the estimated sample size was 14 for each group. Considering a potential dropout rate of 30%, the estimated sample size is 20 for each group. However, this sample size may not have enough statistical power for testing secondary hypotheses related to variables of other non-motor symptoms and/or serum biomarkers. Therefore, we propose to enroll 30 participants in each of the intervention arms.

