### 5.2. Statistical Analysis

Descriptive statistics including mean, standard deviation, frequency, and percentage will be calculated. Mean changes between the three-time points (baseline, post-intervention, and 6-month follow-up) in the experimental and control groups will be examined by two-way mixed-design analysis of variance (ANOVA). If no significant interaction is observed, the main effect will be analyzed using two-tailed t-tests with Bonferroni correction for groups and repeated measures ANOVA for time. Correlation coefficients (r) will be utilized to find relationships between variables including non-motor symptoms and inflammatory biomarker levels. Duration of PD will be used as a covariate in the analysis. The level of significance is set at 0.05. In addition, sub-group analysis based on demographic (e.g., sex and age) or clinical (e.g., Hoehn and Yahr stage and disease duration) information will be conducted.

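### Two post-randomisation withdrawal criteria, combined with a three-visit ANOVA, leave the primary comparison exposed to attrition bias of unknown direction and size

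*Protocol article*

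**What the plan says.** Protocol article, section 2.4.3 has five withdrawal or termination criteria. The first three are death, withdrawn consent and physician discretion. The fourth is "major changes in PD medications or other non-motor symptom medications" and the fifth is "failure to comply (due to hospitalizations, vacations, etc.) with prescribed exercise". The section does not say whether meeting a criterion ends the exercise, the outcome assessments or both.

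Section 2.1 plans a baseline visit, a post-intervention visit within two weeks of the end of the 12-week programme, and a later one: "The assessments will be completed again six months after the end of the intervention period".

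Section 5.2 states that mean changes across these three time points in the two groups "will be examined by two-way mixed-design analysis of variance (ANOVA"). Section 5.1 deals with loss only through the sample size. It reads "With a statistical power of 80% and a Type I error rate at 0.05, the estimated sample size was 14 for each group", then allows for 30% dropout to reach 20 per group, and finally sets enrolment at 30 per group.

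**The concern.** The exercise is prescribed only after assignment, so the compliance criterion can act only on randomised participants. The medication criterion can also be met at any time after randomisation. Neither event is neutral:

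- Section 2.4.2 gives sleep, anxiety and depression drugs as examples of non-motor symptom medications, and section 2.2 names sleep quality, anxiety and depression as outcomes. A participant whose sleep worsens enough to prompt a major drug change could be removed because of the primary outcome.
- Compliance is a consequence of the assigned exercise. Section 3.1 describes behavioural coaching for low adherers in the Qigong arm, and section 3.2 describes none for the sham arm. Unequal removal is therefore possible, though not shown.

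If such people leave the study and the model uses only those with all three visits, the comparison is no longer between the groups as randomised. A later analysis plan cannot recover outcomes that were never collected.

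**Working it through.** **1. The plan's own figures.** Inputs from section 5.1: difference 11.5 points, SD 10.7, power 80%, type I error 0.05 (taken as two-sided), dropout 30%.

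n per group = 2 × [SD × (z₀.₉₇₅ + z₀.₈₀) / Δ]² = 2 × [10.7 × (1.960 + 0.842) / 11.5]² = 13.59, rounded up to 14. Then 14 / (1 − 0.30) = 20. Both stated figures are reproduced. The inflation from 14 to 20 means that the trial is sized on those who remain.

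**2. Is the loss a power problem?** With 30 enrolled per arm and 30% lost, 30 × 0.70 = 21 remain. Power for 11.5 points at SD 10.7 falls from 0.986 to 0.936 (normal approximation), or from 0.984 to 0.925 (t-test). Power stays adequate for the planned effect. The extra enrolment covers precision and does nothing about bias.

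**3. The texts side by side.** Section 2.4.3 puts criteria 4 and 5 in one list with death and withdrawn consent. No section says that participants who meet them are still assessed. Section 5.2 names a mixed-design ANOVA over three time points. In its classical form this needs a value at each time point for every person, so missing only the 6-month visit also removes that person's post-intervention value. Some loss at 6 months is plausible: the phone script in Table A1 describes about 11 visits over 14 weeks and asks about medication changes over three months, while participation lasts about nine months (12 weeks plus six months).

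**4. Illustration A (assumed inputs, no true effect).** Suppose that 30% of each arm would have a PDSS-2 change worse by a gap g than the rest, and that all removals come from this group. If a fraction q of an arm is removed, the poor-change share among those left is (0.30 − q) / (1 − q).

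- q = 0.10: 0.20 / 0.90 = 0.222
- q = 0.30: 0 / 0.70 = 0

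Spurious difference = 0.222 × g:

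- g = 5: 1.11 points, and 1.11 / 3.44 = 32% of the improvement MCID quoted in section 4.2
- g = 10.7 (one SD): 2.38 points, and 2.38 / 3.44 = 69% of it

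The error favours whichever arm loses more poor responders. With equal q in both arms it is zero.

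**5. Illustration B (another assumed mechanism, no true effect).** Change is normal with SD 10.7, and removal depends on a latent variable correlated ρ with poor change. For a removed fraction f, the mean shift among those left is ρ × 10.7 × φ(z) / (1 − f), with z the upper-f normal quantile. For 30% versus 10% the bracketed difference is 0.497 − 0.195 = 0.302. The type I error was simulated with a two-sample t-test on change, starting from 30 per arm.

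| ρ | Spurious difference (points) | Simulated type I error |
|---|---|---|
| 0.2 | 0.65 | not run |
| 0.3 | 0.97 | 0.059 |
| 0.5 | 1.61 | 0.084 |
| 1.0 | 3.23 | 0.25 |

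With 30% removed from both arms by the same mechanism, the difference is 0 and the type I error at ρ = 0.5 is 0.049.

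**The case against.** The strongest reply is that the article does not say what this point fears. It never states that the analysis is restricted to complete cases or to completers, nor that data collection stops. Imputation before the ANOVA would be compatible with section 5.2. Analysis sets and missing-data handling commonly sit in an analysis plan or full protocol that is not shown, so their absence is not a fault. Withdrawal or termination could also mean stopping the exercise only.

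This stands in part. Complete-case analysis is an inference from the named method, and leaving the study is the more natural reading of a list that includes death and withdrawn consent, but it is not certain. What remains is what the article itself fixes: two outcome-related withdrawal rules with no provision for continued assessment, and a model that in its usual form cannot use partial data.

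Four stronger readings are tempting, and the documents do not support them:

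- **A 43% overstatement.** A reader might compute 11.5 / (0.7 × 11.5) = 11.5 / 8.05 = 1.43. That assigns the whole 30% to withdrawn Qigong participants with exactly no benefit. Section 5.1 gives 30% only as a potential dropout rate, with no causes.
- **Eighteen of 60 lost despite having week-12 data.** 0.30 × 60 = 18 is a ceiling, reached only if every loss falls after the post-intervention visit. The same people cannot also be the ones withdrawn before it.
- **A self-contradiction over attrition bias.** The introduction faults earlier trials for missing information on this and other matters. That is a reporting complaint, so it is not contradicted by the rules here.
- **Every trigger is informative.** Only major medication changes count, and the examples of non-compliance include vacations, which need not depend on arm or outcome.

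Finally, participants and assessors are to be blinded and the sham uses the same movements, so a threefold imbalance in removal is not an obvious default.

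**Conclusion.** The point holds as an exposure to attrition bias. As written, two withdrawal criteria can take randomised participants out for reasons linked to arm and outcome, nothing provides for assessing them afterwards, and the classical form of the named ANOVA would also discard partial data.

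The article gives neither the direction nor the size of the bias. The figures of 1.1 to 2.4 points (illustration A) and 0.65 to 3.23 points (illustration B) rest wholly on an assumed 10% versus 30% removal and on an assumed link between removal and outcome. They show that the error could be a material part of the 3.44-point MCID; they do not predict it. With equal removal by the same mechanism and no true effect, there is no bias. The matter should be settled before data collection ends, because the lost outcomes could not be recovered later.

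**What to change.** 1. In section 2.4.3, state that meeting criterion 4 or 5 does not by itself end outcome assessment. These participants are invited to the post-intervention and 6-month assessments already planned, unless they withdraw consent. Criterion 3 (physician discretion) and all treatment decisions stay unchanged.
2. In section 5.2, analyse all randomised participants in their assigned arm with a likelihood-based repeated-measures mixed model that uses every available visit. The planned covariate, duration of PD, can stay. Such a model relies on data being missing at random given what was observed, so step 1 matters more than the change of model.
3. Add a sensitivity analysis for medication changes, which section 4.1 already has participants report.
4. Keep the analysis of compliant completers as supportive only.

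The cost is an amendment to two criteria and to the analysis paragraph, and some effort to bring back participants who have stopped the exercise. No new visits are needed. The estimate may be less favourable than one based on compliant completers.

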### 2.5. Recruitment and Screening

Participants will be recruited primarily from the Parkinson’s Disease and Movement Disorder Center at the University of Kansas Medical Center, in which approximately 200 new and 1400 returning individuals with PD are seen annually. Among individuals with PD being seen, we expect about two thirds will meet our recruitment criteria. Individuals who indicate an interest to participate in research will be contacted by a member of our team. Physician’s permission will be obtained prior to an individual’s participation in the study.

An initial screening will be conducted via phone by members of the research team using a screening script (Table A1).

